#### Additional analyses

The secondary endpoints will be compared between treatment groups by the Student’s *t* test, Wilcoxon rank sum test, Pearson’s χ^2^ test, or Fischer exact test as appropriate. We cannot rule out the possibility that pancreatic duct stents are placed. If that scenario plays out, we will perform a sensitivity analysis of the primary endpoint in two subgroups, namely patients that only received rectal NSAIDs and patients that received combination therapy with pancreatic duct stents. Furthermore, we will conduct a sensitivity log-binomial regression analysis of our primary endpoint in which we adjust for stratification by site. Finally, the costs and effects of both treatment strategies within the 6 months of follow-up will be compared. Cost-effectiveness will be expressed as costs per patient with poor outcome (severe morbidity and/or death) and costs per quality adjusted life year up to 180 days after randomization. Healthcare costs are registered on structured CRFs. Unit prices according to the handbook of the Dutch Health Council are used [28, 29]. Productivity costs are measured by iMTA PCQ and quality adjusted life years by the EQ-5D questionnaire [24, 27]. The cost-effectiveness analysis will be reported separately from the primary study manuscript.

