**Fig. 1 Fig1:**
[figure not shown]
SPIRIT schedule of enrolment, interventions, and assessments. *Baseline variables: age, sex, comorbidity, American Society of Anesthesiologists score, ERCP indication, PEP risk factors, use of pancreatic duct stents. ^Primary outcome: post-ERCP pancreatitis. ^#^Secondary outcomes: incidence of delayed PEP (> 24 h after ERCP), severity of PEP, other ERCP complications, hydration-related complications, length of hospital and intensive care unit stay, health-related quality of life, cost-effectiveness, and exocrine and endocrine pancreatic insufficiency

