### Treatment arms and co-interventions

Eligibility of all potential participants will be discussed with the central study coordinator. After written informed consent, patients are randomized to either the control or intervention group. The control group will be administered 100 mg of indomethacin or diclofenac within 30 min before or after ERCP and no hydration or mild hydration with normal saline, with a maximum of 1.5 mL/kg/h or 3 L/24 h;. After 24 h, the volume and nature of intravenous infusion is at the discretion of the treating physician. The intervention group will be administered 100 mg of indomethacin or diclofenac within 30 min before or after ERCP and periprocedural hydration with lactated Ringer’s solution, 20 mL/kg within 60 min from the start of ERCP (endoscope-mouth contact), directly followed by 3 mL/kg/h for 8 h. Thereafter, the volume and nature of intravenous infusion is at the discretion of the treating physician.

The type, dosing, and timing of rectal NSAID application follow the recommendations of the ESGE [4]. Current ERCP guidelines give no indication for hydration in the control group. Therefore, the hydration schedules in both the intervention and control group are based on the favorable results seen in Buxbaum’s pilot study [16].

To ensure timely delivery of the 60 min bolus, pressure bags or double infusion pumps will be used. The hydration is maximized in patients with morbid obesity (body mass index > 40), because their altered physiology is characterized by a decrease of lean body in tissue water content [17]. Therefore, in these patients, a maximum amount of fluid is calculated by using a fictive maximum weight (FMW) associated with a body mass index of 40 kg/m^2^. The FMW is calculated as follows:$$ FMW=40\ {\left( patient\ length\ in\ meters\right)}^2 $$

The FMW is inserted in the fluid equations of the intervention group.

If the clinical condition of patients in the control group does not allow the infusion restrictions (e.g., in case of hypovolemic shock), higher volume infusion is allowed at the discretion of the treating physician. Furthermore, if patients in the intervention group develop signs of fluid overload, the intensive hydration will be stopped and, if needed, diuretics will be started.

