General treatment measures include a fasting state before ERCP. Antibiotic prophylaxis, measures to correct coagulation disorders and diet reintroduction after endoscopic sphincterotomy will be managed according to a local protocol. We did not encourage the use of pancreatic duct stents to prevent confounding with the intensive hydration regimen. After ERCP, all patients will be hospitalized for a minimum stay of 24 h for timely diagnosis of adverse events and monitoring of intravenous fluid volumes. Longer monitoring, hospitalization, and treatment of adverse events is at the discretion of the treating physician. Post-ERCP pancreatitis will be treated in accordance with the International Association of Pancreatology/American Pancreatic Association guidelines for treatment of acute pancreatitis [18].

To improve adherence to the trial protocol, involved staff members (gastroenterologists, residents, physician assistants, endoscopy nurses, ward nurses and sedationists) in all participating centres will receive specific training in the trial’s standard operating procedures (SOPs). In coordination with the local principal investigator, the SOPs are adapted to the local hospital setting, while ensuring adherence to the trial protocol. Furthermore, the SOPs will be readily available on all wards and on the dedicated FLUYT trial website. The trial coordinator is on call 24/7 to assist in case of any questions. Protocol adherence is evaluated regularly in participating centres.

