### Blinding

Patients and treating physicians are not blinded for treatment allocation (see Discussion). However, a blinded adjudication committee will assess and weigh all events (severe complications and mortality) and decide whether the pre-specified definitions of the primary and secondary endpoints are met. The adjudication committee consists of six gastroenterologists with extensive ERCP experience, a radiologist and a nephrologist. On the basis of primary source data, each member will individually evaluate a patient’s disease course. Disagreements are resolved in a plenary consensus meeting. A final analysis will only be performed after consensus has been reached on each individual endpoint for each individual patient.

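### The planned stent split compares arms within subgroups formed after randomisation: it should be labelled descriptive, and stent use should not be listed as a baseline variable

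*Protocol article*

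**What the plan says.** The article takes these positions on stents:

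- **Policy** (Treatment arms and co-interventions): "We did not encourage the use of pancreatic duct stents to prevent confounding with the intensive hydration regimen". No rule fixes who may or may not receive one, and the Additional analyses section concedes: "We cannot rule out the possibility that pancreatic duct stents are placed".
- **Analysis** (Additional analyses): in that event the plan is "a sensitivity analysis of the primary endpoint in two subgroups, namely patients that only received rectal NSAIDs"; the second subgroup consists of those who were also stented. It is called a sensitivity analysis and carries no caveat about when the stent decision is made.
- **Baseline status**: the Fig. 1 caption lists "PEP risk factors, use of pancreatic duct stents" among the baseline variables. The Descriptive statistics section reports other prophylactics, mainly stents, alongside the baseline characteristics.
- **Timing** (Treatment arms and co-interventions): "After written informed consent, patients are randomized to either the control or intervention group". The intervention bolus is "20 mL/kg within 60 min from the start of ERCP (endoscope-mouth contact").
- **Blinding** (Blinding): "Patients and treating physicians are not blinded for treatment allocation". The Discussion adds that blinding of treating staff was piloted and given up.
- **Link with risk and outcome** (Background): a European guideline keeps stents for high-risk patients, and a meta-analysis gives an odds ratio of 0.35 for pancreatitis with stents.

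The primary analysis is by intention to treat and does not condition on stents.

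**The concern.** Stent receipt is settled after allocation, can respond to allocation, and is related to the risk of the outcome. Comparing arms within levels of such a variable gives up the balance that randomisation provides. If high-risk patients are stented less often when they are known to be receiving vigorous hydration, more of them stay in the unstented hydration group than in the unstented control group, and the two groups are no longer alike.

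Listing stent use as baseline compounds this. A difference in stenting between arms would then look like chance imbalance, when it could be a response to the allocated treatment.

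The label is also inapt. Two subgroup estimates do not test whether the all-patient estimate survives a change of assumption or method. The site-adjusted log-binomial model in the same section does. What is at stake is how the NSAID-only result would be read, because it looks like the direct answer to the trial's question about hydration added to rectal NSAIDs.

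**Working it through.** **1. Order of events.** Consent comes first, then randomisation, then endoscope-mouth contact (when the bolus starts), then any stent during the procedure, then assessment of pancreatitis. On the article's own timeline stent use cannot be a baseline variable.

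**2. The plan's own figures.** No stated figure bears directly on this point. The sample size is used only to scale the illustration. For 8% against 3.2%, two-sided 5% and 80% power, with mean rate 0.056:

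n = [1.96·√(2·0.056·0.944) + 0.8416·√(0.08·0.92 + 0.032·0.968)]² / 0.048² = 359 per arm, or 718 in total. Then 718 × 1.15 = 825.7, giving 826 (413 per arm). Both agree with the article.

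**3. Illustration of the selection effect.** Apart from the overall 8%, every input is an assumption. Hydration has no effect; a share h = 0.20 of procedures is high-risk with 20% pancreatitis; the rest have 5% (0.2 × 0.20 + 0.8 × 0.05 = 0.08). Only high-risk patients are stented, with probability s that may differ by arm. Risk among the unstented is

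R(s) = [0.8 × 0.05 + 0.2 × (1 − s) × 0.20] / [0.8 + 0.2 × (1 − s)]

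| s control / hydration | R control | R hydration | Spurious RR |
|---|---|---|---|
| 20% / 20% | 0.072/0.96 = 7.50% | 7.50% | 1.00 |
| 20% / 10% | 0.072/0.96 = 7.50% | 0.076/0.98 = 7.76% | 1.03 |
| 40% / 20% | 0.064/0.92 = 6.96% | 0.072/0.96 = 7.50% | 1.08 |
| 50% / 25% | 0.060/0.90 = 6.67% | 0.070/0.95 = 7.37% | 1.11 |
| 25% / 50% | 7.37% | 6.67% | 0.90 |

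The last row reverses the one above it: the direction depends on which arm is stented more.

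**4. A second set of assumptions.** With 25% of patients at 15% risk and the rest at (0.08 − 0.25 × 0.15)/0.75 = 5.67%, stenting 30% of high-risk control patients against 10% of high-risk hydrated patients gives 7.43% against 7.82%, RR 1.05. At 50% against 10% it is 7.00% against 7.82%, RR 1.12. Equal stenting again gives 1.00.

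**5. Size against sampling error.** In the 50%/25% row, 413 × 0.90 ≈ 372 control and 413 × 0.95 ≈ 392 hydrated patients are unstented, with about 25 and 29 events. The standard error of log RR is √(1/25 − 1/372 + 1/29 − 1/392) ≈ 0.263, so the approximate 95% interval around 1.11 is 0.66 to 1.85. The planned effect is 3.2/8 = 0.40.

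**6. The stented subgroup.** Because the model stents only one risk class, it shows no bias there. Bias would arise if different kinds of patient were stented in the two arms. Precision is poor in any case: at assumed stent shares of 5%, 10% and 20% there are about 21, 41 and 83 patients per arm, with approximate power for 8% against 3.2% of 10%, 15% and 27% (normal approximation, rough with so few events).

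**The case against.** The case for the plan has several parts.

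- **Bias is conditional.** Patients keep their allocated arm within each subgroup, and bias needs stenting to depend on that arm. A reader might infer that both subgroup estimates are necessarily biased; the article does not support that. This stands.
- **Awareness of the arm is inferred.** The Blinding section speaks of treating physicians, and the data collection section lists the endoscopist separately. A reader might take unblinded endoscopists as a stated fact. It is a strong inference, because the trial is open label and the bolus runs during the procedure, but it is not stated.
- **The effect is small and built on chosen inputs.** This stands. Stents are not encouraged in either arm, and the illustrated bias lies well inside sampling error. If hydrated patients are stented less, it works against hydration and would not create a false benefit.
- **The analysis is conditional and claims little.** It sits under additional analyses, and no inference from it is promised. This stands, and limits the weight of the point.
- **The motive is reasonable.** Unequal stenting could blur the effect of hydration. In the second set of assumptions, with the cited odds ratio of 0.35 for stents and 30% against 10% stenting, the all-patient RR would be 1.06 with no direct hydration effect. That is a consequence of the strategy as delivered, in a comparison that is still randomised. Splitting on stent receipt does not remove it; it replaces it with a selected comparison.
- **The analysis plan may deal with it.** This does not stand. The article itself fixes the subgroups, the sensitivity label and the baseline status of stent use. These are stated choices, not omitted detail.

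**Conclusion.** The point holds as a limited one. The subgroups are defined by a discretionary act after randomisation that is linked to risk and outcome, so randomisation does not protect the comparison within them, and the baseline listing conflicts with the article's own timeline. Whether there is bias depends on differential stenting, on which the article is silent. Under the main set of assumptions, twofold differences in stenting give a spurious RR of about 1.03 to 1.11 among unstented patients (0.90 with the 50%/25% pattern reversed), and equal stenting within risk classes gives none.

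A reader might go further and conclude that the trial's main result is compromised. It is not: the all-patient intention-to-treat analysis does not condition on stents. The correction is still worth making, because it costs almost nothing and prevents a selected estimate being read as a randomised one.

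**What to change.** 1. Move stent use out of the baseline variables in Fig. 1 and the Descriptive statistics section, and report it by arm as a post-randomisation co-intervention.
2. State that the all-patient intention-to-treat analysis is the only basis for inference about hydration added to rectal NSAIDs.
3. Drop the sensitivity label from the stent split, and mark any stent-stratified result as descriptive and non-randomised.
4. If subgroup inference is wanted, use an interaction test on a factor fixed before randomisation and already collected, such as ERCP indication or patient-related risk factors for pancreatitis. Any risk factor that becomes known only during the procedure would bring the same problem back.

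The cost is a change of wording, with no change to sample size, conduct or data collection. At publication 515 of 826 patients had been randomised, so the change could be made before the final analysis. The sponsor gives up reading the stent split as a randomised estimate and may add one modest analysis.

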### Safety

All adverse events, regardless of a supposed connection to the trial, will be reported to the study coordinator. In turn, the coordinator reports adverse events to the Central Committee on Research Involving Human Subjects (CCMO) according to the CCMO directive (death within 24 h, other serious adverse events within 15 days after the sponsor has first knowledge of the event). All serious adverse events will be followed until they have abated or until a stable situation has been reached.

To monitor patient recruitment and safety, an independent data safety monitoring board (DSMB) will be appointed (see Acknowledgments for details). Plenary DSMB meetings will be held after inclusion of 50, 150, 413 (interim analysis), and 650 patients. The DSMB has access to the unblinded patient data and discusses all serious adverse events. These events will be tabulated and a narrative of the complete case will be provided. All deceased patients will be evaluated by the DSMB for cause of death and whether this is related to a study intervention. After every meeting, the DSMB reports to the trial steering committee. A copy is sent to the ethical committee.

A one-sided interim-analysis of the primary endpoint will be performed when 50% of patients (*n* = 413) have been randomized and discharged. Based on the raw data of every patient, a blinded adjudication committee will determine if the criteria for the primary endpoint are met. The interim-analysis will be performed by a blinded, independent statistician who will report to the DSMB, which has access to unblinded data. The advice of the DSMB will be sent to both the ethics boards and the steering committee. Finally, the steering committee decides whether the FLUYT trial should be continued. The Peto approach is used for beneficial effect. For harm (higher incidence of the primary endpoint in the intervention group) no stopping rule is chosen. The trial will be terminated using an upper stopping boundary at *P* < 0.001.

## Discussion

The FLUYT trial will answer the question of whether combination therapy with periprocedural hydration and rectal NSAIDs significantly lowers PEP incidence compared to NSAID monotherapy. Although several RCTs [12, 30, 31] have investigated the value of periprocedural hydration, they have several shortcomings.

First, only two trials [30, 31] combined periprocedural hydration with standard-of-care PEP prophylactics such as rectal NSAIDs. Because of the solid evidence favoring rectal NSAID use in average- to high-risk patients [4, 7] and an accumulating evidence base for routine use in all patients [32, 33], patients must not be withheld rectal NSAIDs.

Second, the trials had small sample sizes ranging from 26 to 510 patients, increasing the chances of type I and II errors and resulting in a power that is too low to reliably investigate an infrequent complication like PEP. This could explain some unexpected findings that are not in line with the current literature; for instance, two RCTs found no significant difference between placebo and rectal NSAID groups [30, 31]. The FLUYT trial includes 826 patients in two parallel groups, which gives us adequate power to detect a potential difference. Furthermore, our multicenter setting allows for a higher generalizability of results.

Third, many trials deviated from the Cotton criteria to classify PEP [19]. Instead, they defined PEP as abdominal pain and hyperamylasemia, but these symptoms are common after ERCP [34]. For a proper diagnosis according to Cotton, both items should still be present 24 h after ERCP and hospitalization should be prolonged for at least 2 nights. The use of a less stringent PEP definition might result in an overestimation of PEP incidence. In the FLUYT trial, we strictly adhere to the Cotton criteria and all patients are hospitalized for 24 h. Not only does this ensure timely recognition and treatment of adverse events, it also allows for a precise assessment of the primary endpoint by physical examination and measurement of amylase and/or lipase 24 h after ERCP.

The design of the two trials that did use combination therapy do not allow conclusions regarding periprocedural hydration. One trial [30] used a four-arm parallel group design in which all trial arms received 1 L over 30 min prior to ERCP. There was no control group without hydration and, therefore, the additive value of hydration cannot be assessed. The other trial [31] used a conservative hydration schedule of 1 L over 2 h before ERCP and 2 L over 16 h thereafter. This could explain the absence of a significant difference in PEP incidence between the hydration and control groups. The study group design in the FLUYT trial allows a proper evaluation of periprocedural hydration. With respect to fluid type, there is evidence suggesting that lactated Ringer’s solution is preferable in the treatment of acute pancreatitis [18]. Therefore, we chose to compare lactated Ringer’s to a control of normal saline. With respect to fluid volume, the vigorous hydration in our intervention group is expected to result in a significant fluid difference of 1.4 L directly after ERCP and 2.3 L after 9 h (for a 75 kg patient undergoing a 1 h ERCP).

A potential drawback of the FLUYT trial design is the lack of blinding. However, we presume that the large difference in fluid administration will lead to a notable difference in a patient’s urine output. Furthermore, we performed a pilot in which treating staff were blinded for treatment allocation. It was concluded that the blinding procedure would be both unfeasible (with respect to the multicenter setting) and undesirable (with respect to breaking the blinding in case of hydration-related complications). Therefore, a blinded adjudication committee will assess the occurrence of all primary and secondary endpoints.

The 9 h hydration schedule used in most trials raised concerns about its cost-effectiveness. For many hospitals, the schedule could prove difficult to adopt in an outpatient ERCP practice [35]. To address this issue, we will perform a separate cost-effectiveness analysis if our trial finds a significant reduction in PEP incidence in the hydration group.

Several choices in the FLUYT trial design, including hydration schedule, fluid type, and sample size, maximize the power of finding a difference in post-ERCP pancreatitis if such a difference really exists. Therefore, we can answer the question of whether periprocedural hydration provides additional protection against PEP on top of rectal NSAIDs and whether this approach is cost-effective.

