**Methods:**

The FLUYT trial is a multicenter, parallel group, open label, superiority randomized controlled trial. A total of 826 moderate- to high-risk patients undergoing ERCP that receive prophylactic rectal NSAIDs will be randomized to a control group (no fluids or normal saline with a maximum of 1.5 mL/kg/h and 3 L/24 h) or intervention group (lactated Ringer’s solution with 20 mL/kg over 60 min at start of ERCP, followed by 3 mL/kg/h for 8 h thereafter). The primary endpoint is the incidence of post-ERCP pancreatitis. Secondary endpoints include PEP severity, hydration-related complications, and cost-effectiveness.

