### Outcomes

The primary outcome is the incidence of post-ERCP pancreatitis according to the Cotton criteria [19]. The criteria of (1) new onset upper abdominal pain; (2) elevation of pancreatic enzymes (amylase and/or lipase) to more than three times the institutional upper limit of normal; (3) criteria 1 and 2 are present at least 24 h after ERCP; and (4) hospitalization (or extension of planned admission) for at least 2 nights, must all be present.

The secondary endpoints (Additional file 1) are (1) incidence of delayed PEP (PEP occurring > 24 h after the procedure); (2) severity of PEP – this will be reported according to the Cotton criteria [19] and the revised Atlanta criteria [20] since the severity grading differs between the two classifications [21, 22] and both are reported in studies; (3) ERCP-related complications according to the Cotton criteria [19], namely bleeding, perforation, and infection; (4) hydration-related complications, such as pulmonary edema and congestive heart failure; (5) length of hospital and intensive care unit stay; (6) generic health-related quality of life, measured by the EQ-5D and SF-36 [23, 24]; (7) cost-effectiveness; and (8) exocrine (fecal elastase-1 < 200 μg/L) and endocrine (HbA1c > 42 mmol/L) pancreatic insufficiency.

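### The cost-effectiveness analysis is promised without condition in the Methods but made to depend on a significant primary result in the Discussion

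*Protocol article*

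**What the plan says.** The abstract's Methods paragraph names the endpoint: "Secondary endpoints include PEP severity, hydration-related complications, and cost-effectiveness". The Outcomes section lists it as item 7 of the secondary endpoints, and the legend to Figure 1 lists it too. None of the three attaches a condition.

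The section on additional analyses states that "the costs and effects of both treatment strategies within the 6 months of follow-up will be compared". It names two ratios, one per patient with poor outcome and one per quality-adjusted life year up to day 180, and adds: "The cost-effectiveness analysis will be reported separately from the primary study manuscript". Again there is no condition.

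In the Discussion, after raising the cost and outpatient feasibility of the 9 h schedule, the article says: "we will perform a separate cost-effectiveness analysis if our trial finds a significant reduction in PEP incidence in the hydration group". The closing paragraph of the Discussion then says the trial can answer "whether this approach is cost-effective", with no qualification.

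**The concern.** After a non-significant primary result the two rules give opposite instructions: the Methods require the economic analysis and the Discussion drops it. If the Discussion rule is followed, reporting of a declared endpoint depends on the result of another endpoint, which is selective reporting built into the plan.

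The condition also does not suit the question. A non-significant difference in PEP does not settle cost-effectiveness. Healthcare costs, productivity costs and QALYs can differ between the arms whatever the primary p-value, and the Discussion itself raises the cost of the 9 h schedule as the reason for the analysis. The closing promise of an answer could not be kept in a trial with a neutral primary result.

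**Working it through.** **Side by side, after a non-significant primary result**

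| Place in the article | Is the cost-effectiveness analysis done? |
|---|---|
| Abstract, Figure 1 legend, Outcomes item 7 | Yes (listed endpoint, no condition) |
| Additional analyses | Yes (no condition) |
| Discussion, paragraph on the 9 h schedule | No |
| Discussion, closing paragraph | Yes (an answer is promised) |

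**Inputs from the article.** Control rate 8%, intervention rate 3.2%, two-sided 5% level, 80% power, 359 per arm before and 413 per arm after a 15% increase (sample size section); Fisher's exact test (primary analysis section).

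**The plan's own figure.** With pooled variance under the null and mean rate (0.08 + 0.032)/2 = 0.056:

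n = [1.960 × √(2 × 0.056 × 0.944) + 0.842 × √(0.08 × 0.92 + 0.032 × 0.968)]² / 0.048²

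= [0.637 + 0.272]² / 0.002304 ≈ 359 per arm.

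The total is 718, and 718 × 1.15 = 825.7, rounded to 826. The stated sample size reproduces, so no figure in the article is wrong on this point.

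**How often the condition fails.** Let x and y be the event counts in the control and hydration arms, independent binomials with n per arm. The Discussion rule is met when y < x and the two-sided Fisher p-value is below 0.05. Summing exactly over all (x, y):

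- P(done) = Σ P(x) P(y) over the pairs that meet the rule.
- Mean observed risk difference when done = Σ P(x) P(y) (x − y)/n over the same pairs, divided by P(done).

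| True rates | n per arm | P(done) | P(not done) | Mean observed difference when done | True difference | Ratio |
|---|---|---|---|---|---|---|
| 8% vs 3.2% (design) | 413 | 0.831 | 0.169 | 5.28 points | 4.8 points | 1.10 |
| 8% vs 3.2% (design) | 359 | 0.767 | 0.233 | 5.47 points | 4.8 points | 1.14 |
| 8% vs 4.8% (assumed 40% reduction) | 413 | 0.418 | 0.582 | 4.78 points | 3.2 points | 1.49 |
| 8% vs 4.8% (assumed 40% reduction) | 359 | 0.361 | 0.640 | 5.08 points | 3.2 points | 1.59 |

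The two values of n span full retention (413) and the number required before the allowance for drop-out and missing data (359). The 40% reduction is not in the article; it shows what happens if the effect is smaller than planned. The interim look is ignored.

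**The case against.** **The Discussion may mean a different analysis.** The word 'separate' could point to an extra analysis of the outpatient question, leaving the one in the Methods untouched. This is possible but weak. The Methods already say that the cost-effectiveness analysis is reported separately, and the article describes no second one.

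**The Methods govern, and nothing is lost.** The conflict comes from one Discussion sentence. The primary endpoint, its test and the sample size are unaffected, and the economic data are planned for collection whatever the primary result. This stands, and it limits the severity. It does not remove the contradiction.

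**The inflation is not the bias of the cost ratios.** A reader might infer that cost per QALY is overstated by 10% to 14%. The article does not support that. The planned denominators are poor outcome and QALYs, not PEP. Selection on PEP reaches them only through a correlation that the article does not give, and it gives no cost or utility inputs either. In a trial that does reach significance, the estimate is also the same with or without the condition. Deleting the condition adds the missing analyses; it does not correct the ones already done.

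**Two further inferences do not hold.** A reader might think that length of stay would go unreported after a neutral result. It is secondary endpoint 5 and is compared between groups without condition, as is quality of life (endpoint 6); only the economic synthesis is at risk. A reader might also think that the poor-outcome ratio is an error because it is not built on PEP. A clinically weighted outcome is a legitimate choice, and whether the ratios are written as incremental is detail that a condensed article may leave to the full protocol.

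**Conclusion.** The contradiction stands in the current text, and the conditional rule is the one to remove. Its main effect is non-reporting: at the design effect a declared secondary endpoint would go unanalysed in about 17% to 23% of trials, and in about 58% to 64% if the true relative reduction were 40%. These figures assume an 8% control rate, 359 to 413 analysed patients per arm and no interim stop. The inflation of the PEP difference (10% to 14% at the design effect) shows the direction of the selection and is a proxy only.

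The severity is moderate. This is a correction of consistency and selective reporting in one separately published secondary analysis, and the primary conclusion is not affected.

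**What to change.** In the Discussion, delete the condition and state that the cost-effectiveness analysis will be performed and reported whatever the result for the primary endpoint, in line with the section on additional analyses. The two named ratios can stay as they are.

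Only wording changes. Healthcare costs, the productivity questionnaire and the EQ-5D are already part of the planned data collection, so neither data collection nor sample size is affected. The article reports 515 of 826 patients randomized with recruitment continuing, so the rule can be settled before the final analysis. The downside is one economic analysis to write up even after a neutral primary result.
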